# A multi-centre, participant-blinded, randomized, 3-year study to compare the efficacy of Virtual Surgical Planning (VSP) to Freehand Surgery (FHS) on bony union and quality of life outcomes for mandibular reconstruction with fibular and scapular free flaps: study protocol for a randomized phase II/III trial

**DOI:** 10.1186/s12885-025-13505-5

**Published:** 2025-02-27

**Keywords:** Head and neck cancer, Oral cavity, Mandible Reconstruction, Virtual Surgical Planning, Quality of life, Randomized controlled trial

## Abstract

**Background:**

Advanced head and neck malignancies with underlying bony involvement often require aggressive oncological resection of large segments of the oral cavity including the mandible. These patients require vascularized donor osseous free tissue transfer to reconstruct significant defects. Traditionally, the donor bone is harvested on its vascular supply and shaped to the defect in a free hand fashion (FHS). However, virtual surgical planning (VSP) has emerged as a method to optimize reconstructive outcomes and decrease operative time. The goals of this study are to assess superiority of VSP to FHS by comparing bony union rates at 12 months, short and long-term complication rates, reconstruction accuracy, quality of life (QOL), functional outcomes, and economic analysis.

**Methods:**

This is a multicenter phase II/III study randomizing four hundred twenty head and neck patients undergoing mandibulectomy in a 1:1 ratio between VSP and FHS. Intention-to-treat analysis will be performed for patients enrolled but unable to undergo VSP-aided reconstruction. The primary endpoint is bony-union rates at 1 year post-operatively. Secondary outcomes include complication rates, QOL, functional outcomes, and economic burden.

**Discussion:**

This study will provide an assessment of two different surgical approaches to the reconstructive methods of mandible defects using fibular or scapular free flaps on bony-union rates, complications, QOL and economics.

**Trial registration:**

Clinicaltrials.gov identifier: NCT05429099. Date of registration: June 23, 2022. Current version: 1.0 on March 6, 2024.

**Supplementary Information:**

The online version contains supplementary material available at 10.1186/s12885-025-13505-5.

## Background

Vascularized bony free tissue transfer is required to reconstitute mandibular defects caused by extirpation of advanced benign or malignant neoplasms. The fibular free flap (FFF) was first introduced in 1989 by Hidalgo [1] and is the workhorse donor bone for reconstruction of mandibular defects due to its dependable vascular anatomy, ability to perform multiple osteotomies, and ample bony stock for dental implant support. More recently, the scapular free flap (SFF) has gained popularity for mandibular reconstruction due to its reliable pedicle length and diversity in composite flap options including bone, muscle, and multiple skin islands [2]. The harvested donor bone often requires multiple osteotomies in complex 3-dimensional (3D) orientations in order to reconstitute the premorbid mandibular anatomy. Traditionally, the donor bone was harvested in a free hand fashion (FHS), where once the vascular anatomy is isolated and ligated, the donor bone is iteratively cut into one or more segments to recreate the curved contour of resected mandible. Within a reasonable ischemia time, each segment must be accurately shaped to recreate the mandibular contour, while preserving its periosteal blood supply, and maintain good contact with its opposing donor bone or mandibular segment to facilitate bony union. Reported complications rates of non-union are 5–28%, and of plate exposure are 3–46% [3–13]. The accuracy of the reconstruction, and the ability to achieve union has significant impact on cosmetic and functional outcomes including bite force, return to a normal diet, and dental rehabilitation and ultimately quality of life [4, 14–19]. 

Recently, virtual surgical planning (VSP) has emerged as a method to improve reconstructive outcomes with evidence of decreased operative time and improved accuracy and union rates [20–25]. VSP leverages preoperative CT scans of the mandible and donor bone in a controlled setting with quantitative and qualitative feedback to virtually plan the reconstruction. Once a reconstruction is chosen, customized surgical cutting guides are then 3D printed, sterilized, and brought to the operating room and applied intraoperatively to the mandible and donor bone. There are a plethora of observational and retrospective studies supporting the benefits of VSP to improve operating room efficiency and patient outcomes [26–35]. A recent retrospective study comparing 43 FHS patients with 49 VSP patients demonstrated a significantly improved rate of non-union of 18.6% vs. 4.1% respectively [36]. A meta-analysis by Tang et al. (2019) [27] reported a standardized decrease of 1.55 h (95% CI: 1.22 to 1.87, *p* < 0.001) of ischemia time to revascularize the bone graft (8 trials included) and 1.01 h (95% CI: 0.80 to 1.23, *p* < 0.001) in total operative time with VSP. *However*,* there are no RCT studies comparing union rates*,* functional outcomes*,* or long-term outcomes of in-house VSP vs. FHS for mandible reconstruction with the fibula or scapula free flap*,* leading to a lack of evidence of superiority of one method to another.*

Given the lack of consistency amongst Canadian health authorities and US insurance plans in terms of the adoption of VSP, a randomized trial is critical to guide optimal reconstructive strategies. The goal of this randomized phase II/III study is to formally compare VSP to FHS, while also informing the design for optimal VSP strategies.

## Methods/design

This protocol, consent form, and data collection forms have been approved by the Research Ethics Board (REB) at the University of British Columbia (H20-03314), in compliance with the Helsinki Declaration.

### Objectives

The primary objective of the proposed trial is to determine if mandibular reconstruction using VSP results in better bony union rates assessed with postoperative CT scans at 12 months compared to standard FHS reconstruction techniques. Secondary objectives are to compare other short and long-term complication rates, reconstruction accuracy, quality of life, and functional outcomes of VSP and FHS. An economic analysis of VSP will also be performed.

### Primary outcome

The primary outcome is non-union as assessed by two independent radiologists at the Vancouver General Hospital (VGH), blinded to the intervention, based on the 12-month postoperative CT scan. Each apposition (between native bone and the donor bone, or between flap segments) will be assessed as non-union, partial union, and complete union. Cases with a disagreement between reviewers will undergo consensus review, and any persisting disagreements will be reviewed by a third radiologist and classification will be based on the majority vote. The non-union rate was chosen as the primary outcome due to the clinical impact of non-union on the potential development of wound complications [10, 19]. As well, based on a retrospective review of non-union data at the VGH, there is a significant difference in non-union rate between patients who underwent FHS and VSP facilitated oromaxillofacial reconstruction.

### Secondary outcomes

Complication rates: These include short-term and long-term complications such as flap failure, infection, and long-term plate extrusion. Adverse events will be identified during routine follow-up, by chart review and by a structured interview with participants.Operative time, ischaemic time and length of stay will be abstracted from the patients’ medical chart.Structural reconstruction accuracy: These will be measured comparing preoperative versus postoperative CT scans using cephalometric measurements including intracondylar distance and mandibular angles.Quality of Life measurements: The University of Washington Quality of Life Questionnaire (UWQOL), MD Anderson Dysphagia Inventory (MDADI), and The General Oral Health Assessment Index (GOHAI) will be collected to be consistent with other studies in this patient population [36, 37]. The UWQOL is a well-validated instrument for this patient cohort and has been demonstrated to have strong internal consistency (Cronbach’s alpha = 0.86) and reproducibility score of > 0.9035 [38–40]. The MDADI has high internal consistency (Cronbach alpha = 0.96) and test-retest stability ranging from 0.69 to 0.8837 [40]. Functional Outcomes:
Occlusal force (bite force): will be determined using the Dental PreScale System (DPS–Fujifilm Global).Donor site morbidity: will be measured by the Lower-Limb Tasks Questionnaire (LLTQ) or the Disabilities of the Arm, Shoulder, Hand (DASH) Questionnaire, both of which have been validated for patients receiving surgery affecting these areas [41, 42]. Occlusion and jaw freedom of movement will be measured and recorded.Dental implantability will also be assessed and determined post-operatively by an independent oral surgeon, who will be blinded to the interventions on the trial [43]. 
Economic Analysis: This will be performed based on the EQ-5D-5 L survey and a health utilization questionnaire (HUQ). Non-hospital visits will be captured through the HUQ that will be administered during each data collection point. Costs of all health care encounters will be done by usual means (e.g., physician costs from Provincial fee schedules, hospital costs from hospital finance departments, drug costs from the health authority and Provincial schedules). We will examine societal costs through the HUQ which has a section on lost productivity and other ‘out-of-pocket’ costs.

#### Inclusion criteria

Primary diagnosis requiring mandibulectomy with fibular or scapular free flap reconstructive surgery.Individuals over the age of 18.Cognitive ability and language skills that allow participation in the trial.Ability to provide informed consent.

#### Exclusion criteria

Contraindications to surgery such as severe comorbidities including metastatic disease.Individuals who do not have a recent CT scan (at most 30 days prior to their surgery), or individuals who are unable or unwilling to obtain a CT scan at most 6 days prior to their surgery, in order to allow time for guide design and sterilization in-house at VGH.Pregnant or lactating individuals.

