### Interventions

Both patient groups will receive the standard presurgical work-up including CT imaging, quality of life questionnaires, functional evaluation of both donor sites, and a functional evaluation of bite force and jaw mobility.

Experimental arm - VSP: The trial research engineer (RE), located at VGH, will segment the CT data to create a 3D model for surgical planning. During the teleconference between site surgeon (SS) and RE, the RE will load the CT data and the segmented 3D model into the virtual planning environment. With the RE navigating the software, which was created in-house at VGH and used in a previous case series, the SS will determine the extent of the disease and define the resection planes [44–51]. After the cutting planes are created, the RE will use the software to create the reconstruction plan with either the patient-specific fibula or scapula, from which the donor bone will be chosen based on the reconstructive cephalometrics. Once the surgeon is satisfied with the plan, the teleconference will end and the RE will create and 3D print the surgical guides for the mandible, for the fibula or scapula, as well as the 3D computed reconstruction (Fig. 1). The surgical cutting guides will be sterilized at VGH’s Medical Device Reprocessing Department and couriered to the SS. The 3D reconstruction model, not requiring sterilization, will be sent directly to the SS. Prior to surgery, the SS will prebend a titanium fixation plate to the reconstruction model and send it for sterilization at the host’s hospital. The planning process, including shipping, will take at most 6 business days. The SS’s medical office assistant is responsible for receiving the shipments and transferring them to the SS. During surgery, the SS will employ the cutting guides and pre-bent titanium plate (Fig. 2). The mandibular cutting guides will be used to guide the resection, and the pre-bent plate is then applied to the remaining native mandible. Next, either the fibular or scapular cutting guide is applied to harvest the donor bone, which is then secured to the plate, followed by re-vascularization of the flap at the head and neck. If the planned resection cannot proceed (possibly due to extensive tumour growth since the time of surgical booking), the surgical team will note the reason for abandonment and conduct a standard FHS.

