### Allocation: sequence generation and implementation

The surgeons at each site will screen all patients for eligibility at the time of their preoperative appointment. Patients who express an interest in participating will meet with the local site research coordinator (LSRC) during the same visit to review the study. If the patient consents at the time of the clinic visit, all baseline data collection will be done at that time. If the patient consents after the visit the LSRC will arrange for a clinic visit to collect the baseline data. After baseline data collection is complete, the baseline CT scan will be uploaded to the REDCap database and reviewed by the research engineer. After confirmation of eligibility, the RE will access REDCap to randomize the patient. Randomization will be centralized, web-based and concealed using the randomization function within REDCap. Patients will be randomized in a 1:1 ratio. Treatment allocation will be stratified by hospital site and disease type: noncancer/cancer. Permuted blocks of varying sizes will be employed and will be unknown to study personnel. An independent statistician will create the randomization list and upload the list to the REDCap database.

This is a single-blind study as the SS will not be blinded to the intervention since they will be applying the guides during the reconstruction surgery procedure. After the randomization list is uploaded onto REDCap, the LSRC who will be performing the data collection, the radiologists who will be performing the bony union analysis, the oral surgeons/prosthodontists who will be performing dental rehabilitation assessments, and the statistician and statistical graduate students who will be performing the statistical analysis will not have access to the list as they will be blinded to the intervention.

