### Treatment and follow-up

Patients will have their surgery scheduled according to local practice. Those patients randomized to the VSP arm will need a minimum of 6 business days from consent to surgery to allow for the production and shipping of the surgical guides. A comparable delay in the FHS arm will not be present, however most patients wait on average 3–4 weeks between consent and surgery.

Participants will be followed during their hospital stay (on average 7–10 days) and at standard clinic intervals (1-, 6-, and 12- months post-surgery) (Table 1).

**Table 1 Tab1:** Schedule of events

Schedule of events	Enrollment			Follow-up				Close-out
	Baseline visit	Allocation	Before surgery	5 days	1 m	6 m	12 m	
Screen for eligibility	X							
Informed consent	X							
Allocation		X						
Screen for adverse events					X	X	X	
Head and neck; abdominal or leg CT scans			X (at least 6 days prior to surgery)	X			X	
Virtual surgical planning; guides 3D printed, sterilized, and shipped to participating sites			X					
Clinical Measurements (jaw mobility, bite force)	X				X	X	X	
Surveys (UW-QOL, EQ-5D-5 L, MDADI, LLTQ/DASH, GOHAI) and HUQ	X				X	X	X	
Data analysis								X
Publication								X

The patient population under study (60% squamous cell carcinoma, 10% ameloblastoma, 7.5% osteosarcoma, 15% osteoradionecrosis, and 7.5% other) have a serious illness and are largely compliant with scheduled follow-up. To maintain desired precision (power), we have incorporated a 5% loss to follow up in our sample size calculation. We anticipate 10% will die within the 1st year of surgery based on the AJCC staging manual and historical site data [52]. Deaths will be considered a competing risk to non-union in the analysis.

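### The CT-timing exclusion caps the interval before surgery although its stated reason needs a minimum; Table 1 sets the opposite bound, and the unit and the 'or' are unclear

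*Protocol article*

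**What the plan says.** All of this is in the protocol article.

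- **Exclusion criteria, first limb:** "Individuals who do not have a recent CT scan (at most 30 days prior to their surgery)".
- **Exclusion criteria, second limb**, joined to the first by 'or': "individuals who are unable or unwilling to obtain a CT scan at most 6 days prior to their surgery, in order to allow time". The sentence gives its purpose as "in order to allow time for guide design and sterilization in-house at VGH".
- **Treatment and follow-up, Table 1**, CT row, before-surgery column: "X (at least 6 days prior to surgery)".
- **Interventions, experimental arm:** "The planning process, including shipping, will take at most 6 business days".
- **Treatment and follow-up, text:** "Those patients randomized to the VSP arm will need a minimum of 6 business days from consent to surgery". The same paragraph puts the average wait from consent to surgery at 3–4 weeks for most patients.
- **Allocation:** the CT is uploaded and reviewed by the research engineer before randomisation. "After confirmation of eligibility, the RE will access REDCap to randomize the patient".

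**The concern.** This rule decides who enters the trial, and as written it works against its own reason. Leaving time to design, print, sterilise and ship guides requires the scan to be *no later* than some point before surgery. The criterion requires it to be *no earlier*. Table 1 has the direction that the reason needs, but it is a schedule of events, and a site screening patients would turn to the eligibility list.

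Two further defects mean that reversing the direction alone would not be enough. The unit changes between sections, and the 'or' makes the two limbs cumulative exclusions when they look as if they were meant as alternatives. At stake are consistent screening across seven centres and, in the VSP arm only, whether guides can be ready by the day of surgery.

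**Working it through.** The plan gives no figure to reproduce. The check has three parts.

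**1. Direction.** Let *D* be the number of days from CT to surgery.

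- Criterion, second limb: *D* ≤ 6.
- Table 1: *D* ≥ 6.
- Both together: *D* = 6 only.

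This holds whichever unit is used, provided it is the same in both places. The first limb uses *at most* 30 days as an ordinary cap on the age of the scan, so nothing in the sentence tells a reader to take the second *at most* in the reverse sense.

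**2. Unit.** Assume a Monday–Friday working week and no holidays. For each weekday of the CT, count (a) the calendar days needed to reach 6 business days and (b) the business days contained in 6 calendar days.

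| Counting rule | CT day | (a) Calendar days for 6 business days | (b) Business days in 6 calendar days |
|---|---|---|---|
| CT day not counted | Mon–Thu | 8 | 4 |
| | Fri | 10 | 4 |
| | Sat | 9 | 5 |
| | Sun | 8 | 5 |
| CT day counted | Mon–Fri | 7 | 5 |
| | Sat | 9 | 5 |
| | Sun | 8 | 5 |

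Example: with a Monday CT not counted, the business days are Tue, Wed, Thu, Fri, Mon, Tue, so the sixth falls 8 calendar days later. The 6 calendar days after that Monday run from Tuesday to Sunday and hold 4 business days.

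If days means calendar days, a CT 6 days before surgery is therefore short of 6 business days by 6 − 5 = 1 to 6 − 4 = 2 business days, on every weekday and under either counting rule. This applies to the criterion's cap and equally to a patient who just meets Table 1's minimum, when production takes its stated maximum.

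If days means business days, Table 1 matches the 6-business-day figures and only the criterion has the wrong direction.

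The clocks also start at different points: the CT (criterion and Table 1), the planning process (Interventions) and consent (Treatment and follow-up). Under Allocation, upload, review and confirmation of eligibility fall between the CT and the start of VSP planning. The article gives no duration for these steps, so no number is attached to them.

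**3. The 'or'.** Let A = has a CT no more than 30 days before surgery, and B = able and willing to have a CT in the 6-day window. As written, a patient is excluded if (not A) or (not B), so eligibility requires A *and* B. Read as alternatives, eligibility requires A *or* B.

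| A | B | As written | As alternatives |
|---|---|---|---|
| yes | yes | eligible | eligible |
| yes | no | excluded | eligible |
| no | yes | excluded | eligible |
| no | no | excluded | excluded |

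The second row is the patient with, say, a 15-day-old scan who cannot be rescanned. The third is the patient without a recent scan who is willing to have one. The second row need not be rare. If the CT is done near consent and surgery follows 3–4 weeks later, the scan is 3 × 7 = 21 to 4 × 7 = 28 days old. That is inside the 30-day limit and outside the 6-day window.

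**The case against.** The best defence is that the intention is easy to see and other provisions protect it.

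- *Central check.* One research engineer, who also plans and prints the guides, reviews every CT before randomising. This stands as a brake on divergence between sites. The article does not say which timing rule the review applies, though, and patients screened out locally may never reach it.
- *Minimum from consent.* The 6-business-day minimum for VSP patients protects lead time whatever the criterion says, at least where the scan exists by about the time of consent. This also stands, but it runs from consent and not from the CT.
- *Usual wait.* An average of 3–4 weeks is 15 to 20 business days at 5 per week, well above 6. Short lead times should be the exception.
- *Days may be shorthand for business days.* This is possible. Neither the criterion nor Table 1 says calendar, so a reader who takes both as calendar days is adding something to the text. The shortfall above is conditional on that reading.
- *The 'or' is read too literally.* Sites probably would treat the limbs as alternatives. For the patient willing to be scanned, a new scan would itself satisfy the 30-day limb once taken, so that exclusion depends on when the criterion is applied. The patient with an older usable scan has no such way out.

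A reader might go further and infer that late guides would push VSP patients into freehand surgery, dilute the contrast under analysis by allocation and cost power. The documents do not support this. They give no rate of late guides. The fallback to freehand surgery is described for a planned resection that cannot proceed, with tumour growth as the example, and late guides are not mentioned. A postponed patient could still receive VSP. Nor do they show that sites following Table 1 would recruit a different kind of patient, because no patient characteristic is tied to CT lead time.

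**Conclusion.** The contradiction is real and lies in current, operative text. The direction of the CT interval in the exclusion criterion is opposed both to the criterion's own reason and to Table 1. That conclusion needs no assumption. The 'or' is defective on its literal reading.

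The unit problem is conditional. If days means calendar days, on a Monday–Friday week without holidays, 6 days fall 1 to 2 business days short of the stated maximum production time, under Table 1 as well as under the criterion. If days means business days, that shortfall disappears and an unstated unit remains.

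The likely effect on the primary comparison is small, given the safeguards above, and cannot be quantified from the documents. The point should be corrected because it governs eligibility and is cheap to put right. It is not a threat to the sample size.

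**What to change.** Reconcile four places: the CT exclusion criterion, the CT note in Table 1, the planning time under Interventions and the minimum from consent under Treatment and follow-up. They should state one direction, one interval and one unit (calendar or business days), consistent with the plan's own production time, and should name the event from which each interval is counted. State explicitly whether the 30-day limb and the new-scan limb are alternatives or both apply. The interval, and the choice between the two readings of the 'or', are for the sponsor.

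The cost is a short amendment to one criterion and one table cell, with matching edits to the lead-time sentences if needed, and one notice sent to all sites together. Sample size, data collection and analysis are unchanged.
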